## Discussion

4

Prior research has demonstrated that VR technology can enhance cognitive abilities, social skills, and life competencies in children with ASD (36). In contrast to the widely used wearable VR devices, this study adopts non-wearable VR technology, specifically selected to reduce physical discomfort and mitigate sensory overload. The VR scenarios included in our intervention are thoughtfully designed to be adaptive, interactive, and engaging, featuring dynamic difficulty adjustments to sustain children’s motivation and interest. To further support engagement and reduce dropout rates, therapists will provide individualized guidance and maintain consistent, ongoing communication with parents throughout the intervention.

As many children with ASD have sensory perceptual deficits, traditional intervention strategies conducted in different environments may heighten their negative emotions (37). Moreover, a significant number of children with ASD experience sensory integration disorders, which can hinder the effective processing of external sensory information in the brain, leading to uncoordinated body functions (38). In this study, non-wearable VR technology will be employed to eliminate specific external stimuli and simplify complex stimuli, thereby enabling children with ASD to focus on a specific scene and respond to specific stimuli. This technology offers a promising avenue for intervention training among children with ASD.

Cognitive-behavioral training with non-wearable VR technology aims to enhance the core symptoms of ASD and improve cognitive abilities, including sensory processing, motor skills, and response inhibition. In one initial clinical trial, VR technology was employed as an adjunctive therapeutic tool in conjunction with Learning Style Profile (LSP). Parental questionnaires, such as the ABC and CARS, were used to assess the efficacy of this approach. The results demonstrated that the VR-augmented treatment yielded more pronounced improvements in core symptoms associated with social deficits, repetitive stereotyped behaviors, and response inhibition in comparison to the control group (39).

In this study, we employed VR training as the primary intervention for the intervention group, and further introduced a two-player game mode to enhance social interaction opportunities. Additionally, the incorporation of pre- and post-intervention assessments is required to facilitate further to explore the effectiveness of interventions for children with ASD, as well as to extend the follow-up period to ascertain the sustainability of the observed effects. In the parent questionnaire, the SDQ will be used to assess the degree to which emotional problems have improved. However, this scale is inherently subjective when completed by parents alone. As such, the ADOS will be introduced by trained researchers to assess symptom improvement. This approach will help to standardize and codify behavioral observations using highly structured observations and tests, thereby enhancing the ability to detect core ASD deficits more effectively. Finally, fNIRS will be employed to assess brain function before and after the intervention, in order to evaluate the impact of VR-based training on brain plasticity, and to understand the neural mechanisms underlying behavioral improvement. To assess the sustainability of treatment effects, participants will complete follow-up evaluations at 24 and 32 weeks post-intervention. These extended assessments will help determine whether improvements in cognitive abilities, social communication, and daily living skills are maintained over time.

### Limitations

4.1

This protocol primarily used three distinct cartoon-based scenarios of interactive play to improve core symptoms in children with ASD. The intervention content focused on general cognitive functions, including attention, response inhibition, and motor coordination, without including more complex or individualized skill domains. Additionally, the training did not target specific skills, and the limited variety of scenarios may reduce engagement over time owing to boredom or loss of novelty. These limitations highlight the need for more flexible and developmentally appropriate training modules that can be personalized to individual therapeutic needs. Future versions of the training system will incorporate a broader range of virtual environments simulating real-world social and adaptive tasks, such as peer interaction, independent eating, toileting, and emotional recognition, with the aim of enhancing communication and daily living skills.

Additionally, the human–computer interaction design of the system remains relatively basic, relying on pre-programmed stimuli and structured response formats. The current absence of real-time adaptability, multimodal feedback (e.g., voice, gesture, facial expression recognition), and context-sensitive interaction limits the naturalistic quality of the VR experience. Enhancing bidirectional interaction and responsiveness is essential for simulating authentic social exchanges and improving user engagement.

The application environment of VR interventions is another important consideration. This training is typically restricted to structured institutional settings, such as hospitals, which may limit accessibility and hinder the generalization of acquired skills to everyday life. To address this issue, future research should investigate the feasibility of portable, home-based delivery formats, such as projector-based systems or augmented reality technologies, enabling children to engage with therapeutic content directly within their natural environments. Integrating intervention tasks into familiar daily contexts may enhance ecological validity and facilitate real-time learning and behavioral transfer. Furthermore, increasing the adaptability of VR systems for in-home use could notably improve user adherence, caregiver involvement, and the long-term sustainability of intervention outcomes for children with ASD.

This study also only included children with an IQ of above 70, which may limit the generalizability of the findings to the broader ASD population, particularly individuals with more severe cognitive impairments. Future studies are warranted to explore the adaptability and effectiveness of VR-based interventions for children with lower cognitive functioning. Further research should also aim to address the limitations identified in this study.

### Conclusions

4.2

In summary, we outline the protocol for a pioneering study aimed at exploring the feasibility and safety of non-wearable VR as a primary therapeutic approach for children with ASD. This cognitive-behavioral training system based on VR technology represents a novel digital therapeutic approach that is convenient, cost-effective, efficient, reproducible, and highly compliant. The system reduces the professional-level requirements for rehabilitation therapists to a certain extent, facilitates their popularization and application, and helps resolve the rehabilitation dilemma faced by many families raising children with ASD.

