**Discussion:**

The primary aim of this trial is to determine the clinical effectiveness of cognitive training using VR technology in children with ASD.

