**Figure 1 f1:**
[figure not shown]
Protocol flow chart of the study. ABC, Autism Behavior Checklist; CARS, Child Autism Rating Scale; SDQ, Strengths and Difficulties Questionnaire; ADOS, Autism Diagnostic Observation Schedule; fNIRS, functional Near-Infrared Spectroscopy.

Participants were enlisted through advertisements in outpatient clinics, kindergartens, community bulletins, and social media platforms. Overall, 160 children aged 4–7 years who met the criteria for ASD, according to the criteria outlined in the Diagnostic and Statistical Manual of Mental Disorders, Fifth Edition (DSM-5), were enrolled. The formal diagnosis was determined using the gold standard instrument, the Autism Diagnostic Observation Schedule, Second Edition (ADOS-2), alongside clinical judgment by experienced psychologists. All participants were between the ages of 4 and 7 years old. Only children who satisfied the eligibility criteria (IQ score of at least 70) for the study were enrolled after completing the Wechsler Preschool and Primary Intelligence Scale (Chinese version) assessment, administered by a professional clinical psychologist. The randomization process was performed using SAS software (version 9.4, SAS Institute).

The primary objective of this study was to create and apply a behavioral training system using VR technology for preschool children with ASD. This system comprises a program utilizing VR technology, a real-time computer monitoring system, and a cloud-based management system. Participants in either the experimental or control group will receive 24 sessions of the intervention model (two sessions per week for 12 consecutive weeks). Participants will be assessed at six time points as follows: before the start of treatment; at 8, 12, and 16 weeks during the treatment period; and at 24 and 32 weeks following the completion of the intervention. The evaluation will follow the guidelines of good clinical practice. The assessment will include questionnaire scales completed by parents, observational scales administered by clinicians, and quantitative fNIRS to measure changes in hemoglobin (Hb) concentration at rest. These include indicators of training, behavioral symptoms, symptom severity, prosocial behaviors, and brain functioning.

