#### Early family intervention

2.8.2

Early family intervention will adhere to the principles of child development. This intervention will entail a comprehensive assessment of each child and the formulation of an intervention program accordingly. The assessment will commence with an examination of each child’s neuropsychological development with the developmental characteristics of ASD. Subsequently, an assessment of the developmental level of children with ASD will be carried out across various domains. The assessment will further encompass an analysis of the family environment and all available resources. Based on the present analysis, an individualized education plan prioritizing social interaction as the core training content and utilizing games as the basic carrier will be formulated. Early family intervention will prioritize the family as the centre of intervention; as such, parents will be the primary implementers of the treatment, with therapists acting as supervisors. The therapist assumes the role of supervisor for the parents and oversees the implementation of the IEP at home. Parents will receive one hour of intervention training per week organized by the therapist. In addition, one hour of training per week will be conducted at home, in conjunction with the classroom video provided by the therapist. The intervention duration will be 12 weeks for each group. Weekly telephone and monthly outpatient follow-ups will be conducted to monitor the implementation of the parental intervention.

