### Risks and adverse events

2.11

Adverse events will be documented throughout the study, and an adverse event reporting system will be established following the guidelines set by the theoretical committee. In the case of serious adverse events, including death, life-threatening symptoms leading to hospitalization or prolonged hospitalization, congenital anomalies/deformities, and permanent or major disability, the investigator will be responsible for reporting the findings to the relevant ethics committee.

This study will concentrate on applying non-wearable VR technology and home-based interventions to enhance core symptoms in children with ASD. The planned intervention does not involve any invasive procedures, and will be delivered through an interactive floor screen or home intervention model, which are unlikely to cause any physical side effects. Additionally, the assessments planned to be used in this study are widely utilized in clinical settings, and are regarded as relatively low-risk owing to their non-invasive characteristics. Previous studies have indicated that cybersickness is a prevalent adverse reaction to VR experiences, manifesting as fatigue, discomfort, and dizziness (34). Prior to beginning the intervention, participants’ susceptibility to cybersickness will be assessed using the Motion Sickness Susceptibility Questionnaire Short Form. Results from this questionnaire will guide an individualized risk assessment to identify children who may have heightened sensitivity to VR-induced discomfort. For those participants without prior experience in VR, introductory exposure sessions will be provided to facilitate gradual adaptation at an individualized, comfortable pace. During the intervention sessions, a trained therapist will closely monitor each participant’s response, promptly adjusting, pausing, or discontinuing sessions if symptoms of discomfort or distress occur. Persistent adverse responses will lead to the child’s withdrawal from the intervention to prioritize their safety and well-being. Additionally, session duration and VR exposure time will be strictly controlled during the intervention and research assessments to prevent potential negative effects stemming from excessive or inappropriate VR usage.

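### Safety is named as an aim, but cybersickness is measured only as susceptibility before treatment and symptoms are actively observed only in VR sessions, so tolerability is not quantified in a standard way and any between-arm comparison is open to ascertainment bias

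*Protocol article*

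**What the plan says.** Section 4.2 (Conclusions) presents the trial as "a pioneering study aimed at exploring the feasibility and safety of non-wearable VR as a primary therapeutic approach". The Discussion paragraph of the abstract states a different priority: "The primary aim of this trial is to determine the clinical effectiveness of cognitive training using VR technology in children with ASD". Safety is therefore a stated aim, but not the primary one.

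Section 2.11 (Risks and adverse events) says of earlier work that "cybersickness is a prevalent adverse reaction to VR experiences, manifesting as fatigue, discomfort, and dizziness". The one instrument it attaches to this risk is given before the intervention starts: "participants’ susceptibility to cybersickness will be assessed using the Motion Sickness Susceptibility Questionnaire Short Form". Its purpose is to identify children at higher risk. The same section says that adverse events will be recorded for the whole study under a reporting system, that serious events go to the ethics committee, that a therapist watches the child during intervention sessions and may modify or stop them, and that persistent reactions lead to withdrawal from the intervention.

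The assessment domains in 2.1 are listed as follows: "These include indicators of training, behavioral symptoms, symptom severity, prosocial behaviors, and brain functioning". The instruments in 2.7 are the ABC, CARS, SDQ, ADOS-2 and fNIRS, with the Wechsler scale for eligibility.

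Both arms receive the family intervention (2.8.2, 2.9). Its regular contacts have a stated purpose: "Weekly telephone and monthly outpatient follow-ups will be conducted to monitor the implementation of the parental intervention".

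**The concern.** A susceptibility score taken before exposure cannot show whether symptoms occurred after exposure. The aim of exploring safety therefore has no matching measurement for the one VR risk that the protocol names.

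The two arms are also observed differently. VR children are watched by a therapist in 24 hospital sessions. In the control arm, parents deliver the treatment and the routine contacts serve another purpose. Fatigue, discomfort and distress can occur in either arm, but the described arrangement makes them more likely to be noticed in one. The observing therapists also know the allocation (2.5).

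The error could run the other way too. The protocol does not say that a session eased for mild symptoms must be entered as an adverse event, so mild reactions to VR may be undercounted.

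What is at stake is the tolerability claim. Reduced discomfort is part of the case for a non-wearable system in the Introduction and Discussion, so readers will look for evidence on it. The primary efficacy analysis is not affected.

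**Working it through.** The protocol gives no safety figure to reproduce. The check sets its provisions side by side and then asks how large the effect of unequal observation could be.

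**Aim against measurement**

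- Aim: safety of non-wearable VR (4.2).
- Named risk: cybersickness, described as fatigue, discomfort and dizziness (2.11).
- Instrument for that risk: a susceptibility questionnaire, before the intervention only (2.11).
- Instrument for symptoms during or after exposure: none named in 2.1, 2.7 or 2.11.
- Active symptom observation: by the therapist in intervention sessions, in a paragraph about VR discomfort (2.11).
- General adverse-event recording: whole study, not limited to one arm (2.11).
- Contacts common to both arms: calls and visits to monitor how parents carry out the programme (2.8.2).

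**Scheduled staff contacts over 12 weeks**

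- Control: 12 weekly parent trainings + 12 weekly calls + about 3 monthly visits = 27.
- VR: 27 + 24 sessions (2 × 12) = 51.
- The week 8 and week 12 assessments (2.1) add 2 to each arm: 29 against 53.

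The difference of 24 consists entirely of sessions in which a therapist watches the child. Control children may also be seen when therapists instruct parent and child together (2.9), so they are not unobserved.

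**Effect of unequal detection**

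Assume the same true event rate p in both arms, with detection probabilities d_VR and d_C. The recorded rates are p × d_VR and p × d_C, so the apparent risk ratio is d_VR / d_C, whatever the value of p. The documents give no detection probabilities. With assumed d_VR = 0.90:

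- d_C = 0.25: 0.90 / 0.25 = 3.6
- d_C = 0.50: 0.90 / 0.50 = 1.8
- d_C = 0.75: 0.90 / 0.75 = 1.2

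With 80 children per arm and an assumed true rate of 10%, the expected recorded counts are 80 × 0.10 × 0.90 = 7.2 in VR, against 2.0, 4.0 or 6.0 in control. Equal detection gives a ratio of 1.0. If mild VR reactions were handled in the session and not recorded, d_VR could fall below d_C and the ratio would be below 1.

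**What a VR-arm count can show**

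With no events among n children and complete recording, the one-sided 95% upper limit is 1 − 0.05^(1/n):

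- n = 80: 3.7%
- n = 72 (the per-group number before the allowance for loss in 2.2): 4.1%

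This limit applies to the recorded rate. If only a fraction d of affected children are recorded, the limit on the true rate is 3.68% / d. That is 4.9% at d = 0.75, 7.4% at d = 0.50 and 14.7% at d = 0.25 (d assumed). The complete-recording limits follow from sample size alone and are not evidence of a defect. They show that the meaning of a low count depends on how symptoms were sought.

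**The case against.** The strongest reply is that this is a journal article. Event forms and elicitation questions usually sit in the full protocol, which is not shown. Section 2.11 commits to adverse-event recording throughout, and 2.1 and 2.7 list effectiveness assessments, so the absence of a safety scale there proves little. Cybersickness arises from VR exposure, so looking for it in VR sessions is appropriate. Section 3 announces no between-arm test of adverse events, and the detection figures above are assumptions.

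Much of this stands. A missing form would not be a finding. The point rests on what the article does state: which cybersickness instrument is used and when, where symptoms are actively observed, and what the common contacts are for. Taken together, these do not deliver a standardised tolerability result for the stated aim. The bias concern is conditional, because it applies only if adverse events are compared between arms.

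Two stronger readings are tempting, and the documents support neither.

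- A reader might infer that no sound safety conclusion is possible. Recording throughout the study, serious-event reporting and withdrawals for persistent reactions would support descriptive statements, including counts for the VR arm.
- A reader might infer that 2.11 contradicts itself, since the intervention is delivered by means "which are unlikely to cause any physical side effects" and, two sentences later, cybersickness is called prevalent. The first statement concerns this floor screen and the home programme. The second reports earlier studies of VR in general, and the Introduction links the problem to head-mounted displays. This is a tension in wording, and precautions against an unlikely event are not inconsistent.

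**Conclusion.** The point holds as a worthwhile improvement to safety recording. As described, the trial can report adverse events, serious events and withdrawals descriptively. It cannot quantify cybersickness in a standardised way, and a between-arm comparison of adverse events would be open to ascertainment bias.

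The size of that bias cannot be derived from the protocol. The spurious risk ratio of about 1.2 to 3.6 rests on equal true rates and on assumed detection of 90% in VR and 25% to 75% in control. It illustrates a plausible scale and is not an estimate. The conclusion also assumes that the full protocol has no symptom checklist or common elicitation that the article omits; if it has one, citing it would settle the matter.

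Timing adds some urgency. Recruitment began on 24 December 2024 and the anticipated end is 30 September 2026 (2.4), and symptoms that go unrecorded cannot be recovered later.

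**What to change.** 1. At the end of each VR session, the therapist already present completes a brief fixed checklist (fatigue, discomfort, dizziness, distress). Every adjustment, pause or discontinuation is recorded against the patient ID and session number. Section 2.8.1 already provides a patient ID and a count of interventions.
2. The same short symptom questions are asked in both arms at the existing weekly calls and monthly visits, starting on the same date in both arms. Any between-arm comparison of adverse events uses only these common contacts.
3. Session-observed events are reported separately as a VR-arm rate with an exact confidence interval. This should be computed per child, because a child's sessions are not independent. The denominator is the children observed after the checklist was introduced.
4. If this is not done, the wording in 4.2 should limit the safety aim to descriptive reporting of documented adverse events.

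These steps change recording only and leave the handling of symptoms as it is. The cost is a one-page form, about a minute more per session and a few questions in contacts already scheduled, with no extra staff or visits. Recorded event rates will be higher than under passive reporting, and the report should say so.
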